### Participants and recruitment

Eligible study participants include AYAHIV, AYAHIV caregivers, HCW, and key informants (KI). The eligibility criteria for the different groups are outlined in Table 1. The schedule for the various study activities for study participants is shown in Table 2.

**Table 1 Tab1:** Inclusion and exclusion criteria and the anticipated sample size of all the CombinADO study participants

Participant	Inclusion	Exclusion	Anticipated sample size
AYAHIV	HIV-positive, per medical records and confirmed by health facility staff Age 10–24 years Registered as a patient at the study site Aware of HIV+ status Provision of signed and dated informed consent form for adolescents aged 18 and above For adolescents aged 12–17, informed assent and parental informed consent to participate in the study For adolescents aged 10–11, parental consent to participate in the study Stated willingness to comply with all study procedures	Has an acute medical condition requiring immediate medical care	*N* = a minimum of 1200 and a maximum of 2400 for the post-intervention assessment *N* = a minimum of 360 and a maximum of 720 exit interviews
Caregivers	Age 18 years and older Attending a caregiver-specific support group Willingness to be audio-recorded	None	*N* = a minimum of 90 and a maximum of 120 semi-structured interviews
HCW	Age 18 years and older Involved in the provision, management, or oversight of adolescent-focused HIV services at the 12 specified study sites Willingness to be audio-recorded	None	*N* = a minimum of 70 and a maximum of up to 112 semi-structured interviews *N* = a minimum of 35 and a maximum of up to 50 costing questionnaires
KI	Age 18 years and older Involved in the provision, management, or oversight of adolescent-focused HIV services at the 12 specified study sites Willingness to be audio-recorded	None	*N* = a minimum of 32 and a maximum of 60 semi-structured interviews

**Table 2 Tab2:** Study assessment schedule for all the CombinADO participants

	Pre-intervention	Intervention implementation	Post-intervention

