### Interventions

The intervention design is based on extensive formative research with AYAHIV, HCWs, AYAHIV caregivers, and other key stakeholders in this setting. Preliminary work included implementation science (quantitative surveys, qualitative interviews) and human-centered design methods, under which AYAHIV and stakeholders including AYAHIV participated in an intensive, iterative process of testing and refinement to develop a multi-component intervention strategy, the CombinADO strategy [14]. Once developed, this strategy was piloted with AYAHIV, caregivers, and HCWs to demonstrate the various intervention components’ acceptability and feasibility. Based on this formative phase’s findings, we designed a multi-component package of intervention modalities that will be delivered as part of enhanced services for AYAHIV at intervention sites. Both the control and intervention conditions will be in place at the study sites for 12 months. A complete list of control and intervention components and each component’s rationale is outlined in Table 3.

**Table 3 Tab3:** CombinADO study arm components during the 12 months of implementation

Component	Rationale	Study arm	
		Control	Intervention
Radio ads	Engaging radio mini shows that address community stigma and medical literacy through busting common myths with humor and building empathy with heartfelt storytelling	X	X
Community sensitization campaign	Large-scale, infographic billboards and posters located in public areas and secondary schools to address stigma and medical literacy and promote community support for AYAHIV	X	X
Informational posters	Large-scale, infographic posters located in clinic waiting areas to normalize HIV and build confidence in treatment	X	X
Motivation walls	Interactive, patient-generated posters located in the consultation room where patients can post words and phrases about themselves and their futures	X	X
Pill boxes	A discreet pill container to support ART adherence	X	X
CombinADO-specific AYAHIV training	Comprehensive in-service training for healthcare workers	X	X
One-stop shop	Combined adolescent and HIV services	X	X
Treatment toolkit	A guide to clinic visits and discussions on Art and viral load monitoring to help HCW better communicate with patients	X	X
Self-reflection kit	A simple handout for providers to help patients reflect on their ART progress and understand the concept of viral load as a measure of ART success	X	X

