Peer support at clinical level	Peer exposure to examples of AYAHIV openly living with HIV and opportunities to share their experiences with HIV in one-on-one interactions with other AYAHIV during clinic visits		X
Informational and motivational video	An informational and motivational video that in simple language with engaging graphics that (a) demystifies and simplifies HIV, ART, and viral load and (b) emphasizes that people can live long, healthy lives		X
Support groups for caregivers of AYAHIV	A learning, support, and empowerment group for caregivers of AYAHIV. Through monthly gatherings, the program aims to foster confidence and equip caregivers with strategies to support AYHIV adherence journey		X
Support groups for AYAHIV	A peer-to-peer learning, support, and empowerment group to address loss of hope and improve medical literacy. Through biweekly gatherings, the program aims to foster belonging and confidence, equipping young people and caregivers with strategies to navigate the adherence journey		X
Mental health screening and linkage to adolescent-focused mental health support	HCWs will be trained in the use of a brief mental health screening tool focusing on depression, anxiety, and post-traumatic stress disorder. Mental health service providers at each facility will be trained and supported to provide diagnostic and mental health support to youth with positive screens who agree to further evaluation		X

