**Secondary**			
To evaluate the efficacy of the CombinADO strategy on the rate of retention in care among AYAHIV receiving HIV care at 12 health facilities in Nampula Mozambique	Retention in care defined as objective evidence of engagement in the preceding 90 days among AYAHIV in care at intervention and control sites	Increases in retention in care is a causal intermediate (mediator) through which the CombinADO strategy may increase HIV viral suppression	Different elements of the CombinADO strategy are likely to support AYAHIV’s retention in care during the intervention period
To evaluate the efficacy of the CombinADO strategy on the rate of adherence to ART among AYAHIV receiving HIV care at 12 health facilities in Nampula Mozambique	Self-reported using the Wilson measure; TDF levels on a subset of participants in care, selected retrospectively in a case-control substudy comparing AYAHIV who have VL < 50 copies/mL, versus those with VL ≥ 50 copies/mL	Increases in ART adherence is a causal intermediate (mediator) through which the CombinADO strategy may increase HIV viral suppression	Different elements of the CombinADO strategy are likely to support AYAHIV’s adherence to ART during the intervention period
To assess the uptake, feasibility, and acceptability of the CombinADO strategy at 12 health facilities in Nampula Mozambique	Uptake and utilization of intervention components by AYAHIV among AYAHIV in care at intervention and control sites; implementation fidelity by health care workers and key informants	Uptake and implementation of the intervention is an intermediate (mediator) through which the CombinADO strategy may increase HIV viral suppression	Inadequate uptake and implementation of the intervention and/or components can limit efficacy of the intervention
To estimate the cost and incremental cost-effectiveness of the CombinADO strategy at 12 health facilities in Nampula Mozambique	Incremental cost per additional case of viral suppression < 50 copies/mL at 12 months	HIV viral suppression provides an objective summary measure of intervention effectiveness	The CombinADO strategy is hypothesized to increase viral suppression through increases in retention in care and/or adherence to ART in the target population

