#### Effectiveness outcomes

The primary outcome is viral suppression < 50 copies/mL at 12 months post-intervention implementation among AYAHIV at intervention and control sites, which will be assessed through real-time viral load testing.

Secondary outcomes include:

(1) ART adherence will be measured by using a validated Wilson self-report ART adherence measure administered on all AYAHIV participating in the one-time post-implementation assessment at 12 months post-intervention implementation [26, 27]. In addition, TDF levels will be measured on a subset of participants in care selected retrospectively in a case-control sub-study comparing AYAHIV who have VL < 50 copies/mL, versus those with VL ≥ 50 copies/mL. The Wilson measure has previously been implemented in this setting to assess ART adherence among AYAHIV during the first phase of the CombinADO study [12]. (2) Retention in care will be measured as objective evidence of engagement in the preceding 90 days among AYAHIV in care at intervention and control sites abstracted from routine clinic records.

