### Data analysis

#### Populations for analyses

The primary outcome (and secondary adherence outcome) will use an intention to treat population of all participants consenting to the post-intervention assessment who complete a questionnaire and VL test. The per-protocol population for the primary outcome (and secondary adherence outcome) will define exposure to the intervention based on AYAHIV-stated engagement in one or more component of the CombinADO intervention during interviews at the post-intervention assessment. The secondary retention in care endpoint will use the eligible (based on inclusion criteria) population of all AYAHIV registered at the clinic site during a 15-month period extending from 6 months before the start of the intervention period to the end of the intervention period. Data for the secondary retention in care endpoint will use routine data abstracted from clinic records. This definition will exclude AYAHIV, who newly initiated ART at the site in the final 6 months before the end of the intervention period.

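### The retention cohort keeps patients already on ART who first register at a site in the last 90 days; their entry visit counts as retention, and their share can differ by arm

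*Protocol article*

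**What the plan says.** The protocol article fixes the retention population under Populations for analyses. It takes eligible patients, namely "all AYAHIV registered at the clinic site during a 15-month period extending from 6 months before the start of the intervention period", and the window closes when the intervention does: "extending from 6 months before the start of the intervention period to the end of the intervention period". One group of late entrants is then removed: "This definition will exclude AYAHIV, who newly initiated ART at the site in the final 6 months before the end of the intervention period".

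The site-related eligibility criterion in Table 1 is "Registered as a patient at the study site". It sets no minimum time at the site and does not require attendance when the intervention starts.

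The outcome, under Effectiveness outcomes, is "objective evidence of engagement in the preceding 90 days among AYAHIV in care at intervention and control sites abstracted from routine clinic records". Table 4 defines it in the same way. Neither place states the date from which the 90 days are counted back.

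On duration, the Interventions section says: "Both the control and intervention conditions will be in place at the study sites for 12 months". Randomization and blinding states that allocation is open to the study team, health workers and patients. Statistical analysis reports risk ratios from a log-link GEE and treats secondary endpoints in the same way as the primary.

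**The concern.** The exclusion of new initiators suggests that the authors saw a difficulty with late entry, but the rule covers only some late entrants. A patient who transfers in on treatment during the last three months has had almost no time to be lost. That patient's first visit falls inside the outcome window, so the result is known at entry.

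Randomisation does not protect against this. Clinics were randomised, and these patients join afterwards, at a clinic whose allocation is not concealed. If the added services drew patients to intervention clinics, those clinics would gain more automatic successes and the endpoint would show a retention benefit that nobody experienced. The opposite imbalance would hide a real benefit.

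A second group sits at the other end of the window: patients registered in the six months before the start who had already stopped attending. Most of the added components reach people who attend; peer support, for example, consists of "one-on-one interactions with other AYAHIV during clinic visits". Such patients could seldom be affected by the randomised difference, yet they count as not retained unless they return.

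**Working it through.** **1. The window.** The stated length is 15 months. Six months before the start plus a 12-month intervention gives 6 + 12 = 18 months, so the stated figure is not reproduced. Two other windows give 15: 3 + 12, and 6 + 12 − 3 (entry closing about 90 days before the end). The article states neither, and its stated end point is the end of the intervention.

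**2. Who is retained by definition.** On the literal text, three late entrants compare as follows:
- New ART initiator at the site in the final 6 months: excluded.
- Already on ART, first registered at the site 4 to 6 months before the end: included, and must attend again to count as retained.
- Already on ART, first registered in the last 90 days: included, and the registration visit is itself engagement within the 90 days, so the outcome is 1. This holds if the look-back is anchored at the end of the intervention.

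**3. Size of the possible bias.** Let p be true retention among everyone else, and c and i the shares of last-90-day entrants in the control and intervention cohorts. Observed retention in an arm with share g is (1 − g)p + g. With no true effect, the spurious difference is (i − c)(1 − p).

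Inputs: p = 55%, the middle of the 50–60% assumed for control clinics under Sample size and power (Retention). The shares c and i are assumptions, because the article gives none.

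- c = 5%: 0.95 × 0.55 + 0.05 = 0.5725
- i = 8%: 0.92 × 0.55 + 0.08 = 0.5860. Difference 1.35 points, RR 0.5860/0.5725 = 1.024
- i = 10%: 0.90 × 0.55 + 0.10 = 0.5950. Difference 2.25 points, RR 0.5950/0.5725 = 1.039

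Across the stated range of p, for i = 8% and 10%:

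| p | Spurious gain (points) | RR |
|---|---|---|
| 50% | 1.5 to 2.5 | 1.029 to 1.048 |
| 55% | 1.35 to 2.25 | 1.024 to 1.039 |
| 60% | 1.2 to 2.0 | 1.019 to 1.032 |

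If c = i, there is no spurious difference under the null.

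**4. Patients lost before the start.** Let a share f of each arm be lost before the start and never return. Then RR = (1 − f)p1 / ((1 − f)p0) = p1/p0, so the planned estimate is unchanged.

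The loss is in precision. Take the article's 220 per site and 6 sites per arm, and borrow the ICC of 0.05 from the primary outcome, since none is given for retention. The design effect is 1 + 219 × 0.05 = 11.95, and the effective size is 1320/11.95 ≈ 110 per arm. For an illustrative true 50% v 68% (RR 1.36), a two-proportion normal approximation gives:
- f = 0: 50.0% v 68.0%, power about 0.78
- f = 10%: 45.0% v 61.2%, power about 0.68
- f = 20%: 40.0% v 54.4%, power about 0.57

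The RR is 1.36 in every row. The values of f and the 18-point effect are assumptions.

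**5. The cohort descriptions.** Populations for analyses takes everyone registered. Table 4 and Effectiveness outcomes restrict the endpoint to patients in care. The retention power paragraph uses 12 × 220 = 2640, which reproduces, but describes these as patients in active care over 12 months. These are different denominators.

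**The case against.** **The bias is speculative and small.** The article gives no transfer rates and does not say that the added services attract transfers. The limitation it acknowledges on contamination between sites does not mention transfers. On the assumed shares the effect is about two points, against true gains of around 18 points that the trial would have power of about 0.8 to detect. All of this stands. It keeps the point modest and confined to a secondary endpoint, but it does not close the gap in the rule.

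**The window may already close early.** If 15 months means 6 + 12 − 3, last-90-day entrants drop out. A reader therefore cannot say that the problem exists whatever window was meant. The stated end point nevertheless contradicts this reading, so the text as written leaves these patients in.

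**The in-care wording may already exclude those lost before the start.** Perhaps, but it conflicts with taking everyone registered. If it means in care at the time of outcome, it is circular.

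**A stronger reading of the early group is tempting.** A reader might infer that pre-start losses bias the result towards no effect, so that a 10-point gain shows as 9 to 7 points if 10 to 30% were lost. That is a risk-difference calculation, and the planned measure is the risk ratio, which equal shares leave unchanged. Randomisation balances these losses in expectation. Their outcome is not fixed by entry date either, since they can return. Keeping them regardless of attendance is a defensible intention-to-treat choice.

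**Conclusion.** The point holds for late entrants. As written, patients already on ART who first register in the last 90 days belong to the retention cohort and are retained by definition. Because they enter after open allocation, an imbalance between arms would bias the risk ratio. On the assumed shares of 5% v 8–10%, with 55% true retention, the spurious gain is 1.4 to 2.3 points (RR about 1.02 to 1.04). This rests on those assumed shares, on a look-back anchored at the end of the intervention, and on the window ending where the text says it does.

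For patients lost before the start, the documents support only a loss of precision and an unclear denominator, not a biased risk ratio. The inconsistencies between 15 and 18 months, and between registered, in-care and actively-in-care patients, are real and leave the cohort not uniquely defined. The point deserves correction before database closure, but it does not threaten the primary outcome.

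**What to change.** 1. In Populations for analyses, tie the late-entry exclusion to first registration at the site for any reason. The minimum is the final 90 days; using the final 6 months already applied to new initiators would give one rule for all late entrants.
2. State the date from which the 90 days are counted back.
3. Keep the cohort as now defined as a sensitivity analysis.
4. Add a sensitivity analysis restricted to patients with evidence of engagement in the 90 days before the intervention start. This should not replace the main cohort.
5. Reconcile the 15-month window with 6 + 12 = 18, and use one description of the denominator in Populations for analyses, Table 4, Effectiveness outcomes and the retention power paragraph.

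The cost is wording plus a date filter on clinic records that are abstracted anyway. Table 5 lists ART start, most recent visit, and pharmacy dispensing and refill information. It does not name the date of first registration, so the team should confirm that this is captured. The main denominator becomes slightly smaller, and the 2640 should be checked against the definition chosen. Entrants after allocation but before the cut-off remain in the cohort, so reporting their number by arm would show whether any imbalance persists.

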#### Statistical analysis

Descriptive statistics will be presented with frequency (percent) or median (interquartile range) depending on the type and will provide overall and by allocation arm. Review of data distributions will be undertaken prior to applying any inferential statistics requiring specific assumptions and methods revised or corrective procedures undertaken. Covariates and specific details of analysis will be fully specified before database closure in a detailed SAP developed by the study statistician and study team. All statistical tests will be two-sided with nominal *α* = 0.05. Study endpoints are binary and will be approached in a similar way. The primary outcome analysis will compare AYAHIV virologic suppression at 12 months post-intervention implementation in intervention versus control sites using generalized estimating equations under a binomial model, with a log link and robust standard errors, providing unbiased marginal estimates of the intervention effect while adjusting for within-cluster correlations. Clustering will be by site using an exchangeable correlation structure. Estimates will be reported as risk ratios (RR) with robust 95% confidence intervals and *p*-values assessed at *α* = 0.05 for all comparisons. No additional adjustment variables will be included in the primary analysis. In subsidiary analyses, we will include covariate adjustment based on confounders selected a priori using direct acyclic graphs. Sensitivity analysis will address potential heterogeneity in clustering by evaluating endpoint models under different assumed correlation structures. Missing outcome data will be handled by complete case analysis in the first case and then by sensitivity analysis substituting alternate outcome values for missing data. Missing data in covariates will be handled by multiple imputations using chained equations. Analysis of secondary endpoints is not conditional on the outcome of the primary endpoint. Secondary endpoints will be approached identically as the primary endpoint. Planned subgroup analyses, which include by age group [10–14, 15–19, 20–24], sex, pregnancy status during the intervention period among females, duration of prior ART use, and ART regimen, will be carried out for primary and secondary outcomes using the same approach as the previously described. Exploratory analyses will include:
For analyses of primary and secondary endpoints, application of generalized linear mixed effects models instead of GEE in the case of heterogeneity between sites.Alternate definitions of endpoints:
Primary endpoint: viral suppression threshold at 1000 copies/mLSecondary outcome (adherence): alternate thresholds to define adherent to ART based on preliminary analysesSecondary outcome (retention): alternate thresholds to define retained on ART based on preliminary analyses

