Survey questionnaire	o Basic demographic information, education, and vocation information o HIV, STI, ART, reproductive health beliefs and literacy o Adherence and adherence self-efficacy o Youth readiness for independent health care o Relationship/marital status o Mental health o Life events o Substance use o Sexual risk o Reproductive health, including pregnancy and parenthood o Interpersonal violence o Partner, family, and social support o HIV stigma/disclosure o Experience with COVID-19 o Uptake of CombinADO strategy intervention components o Feasibility, acceptability, and appropriateness of all strategy intervention components	AYAHIV	T3
Exit interviews	o Experiences and satisfaction with the services received and various intervention components	AYAHIV	T2
Semi-structured interviews	o Perceived benefits and challenges of attending the support groups o Comfort taking part in the support group o Satisfaction with current support groups structure o Recommendations for refining the existing support groups	Caregivers	T2
	o Experience implementing the intervention, including time spent providing care to AYAHIV o Impact of the intervention on facility and delivery of health services o Met and unmet needs of the AYAHIV population seeking services o Adoption, implementation, maintenance, reach, feasibility, acceptability appropriateness, and fidelity of the intervention various components	HCWs and KIs	T1–T3
Costing questionnaire	o The daily schedule at the health facility o Time spent working across various clinic activities, including consultations with AYAHIV	HCWs	T1 and T2
Blood sampling	o Blood for real-time viral testing o Dried blood spot (DBS) samples for TDF-DP drug-level testing	AYAHIV	T3
Abstraction of AYAHIV routine data	o Date of HIV diagnosis o ART start date o Current ART regimen o Intercurrent hospitalizations o Most recent HIV RNA viral load and CD4 results o Pharmacy dispensing and refill information o Most recent visit date o Retention in care	Clinic records	T3

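### The rule that all endpoints are binary and analysed like the primary does not fit the TDF-DP drug level, a concentration measured in a subset selected on viral load

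*Protocol article*

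**What the plan says.** In the protocol article, Statistical analysis fixes the endpoint type for the whole trial: "Study endpoints are binary and will be approached in a similar way". The primary comparison is by arm, "using generalized estimating equations under a binomial model, with a log link and robust standard errors", with site as the cluster and results given as risk ratios. The section then adds: "Secondary endpoints will be approached identically as the primary endpoint".

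Adherence is a secondary outcome with two measures (Effectiveness outcomes; Table 4). One is the Wilson self-report, given to everyone in the post-intervention assessment. The other is a drug level: "TDF levels will be measured on a subset of participants in care selected retrospectively in a case-control sub-study comparing AYAHIV who have VL < 50". The comparison group is those at or above that viral load. Table 5 lists the specimen as "Dried blood spot (DBS) samples for TDF-DP drug-level testing".

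Three further statements bear on the point:

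- Populations for analyses gives the adherence outcome the same population as the primary: all who consent and complete both the questionnaire and the viral load test.
- The adherence paragraph of Sample size and power carries over the primary outcome's assumptions.
- The exploratory list closing Statistical analysis allows other thresholds for being adherent, to be based on preliminary analyses.

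Details are deferred: "Covariates and specific details of analysis will be fully specified before database closure in a detailed SAP". Some flexibility is also kept: "Review of data distributions will be undertaken prior to applying any inferential statistics requiring specific assumptions", with methods revised if needed.

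**The concern.** Viral suppression and retention are each defined in binary form where they are introduced. TDF-DP is introduced as a level. A binomial model can take a level only after it is cut in two, so a blanket statement that endpoints are binary commits the trial to cutting it. TDF-DP is the trial's only drug-level measure of adherence, and Table 4 names adherence as a mediator of the primary effect. A shift in drug exposure that does not carry participants across the chosen line would go unseen.

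The instruction to proceed identically to the primary has a second difficulty. It implies a comparison of arms, whereas the sub-study is described as a comparison by viral load status, and its members are selected on that status. Viral load is the primary outcome and a consequence of adherence. An unweighted arm comparison in such a sample does not estimate the effect of the strategy on adherence, whether the level is cut or left continuous.

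**Working it through.** **1. The plan's own figure.** None is given for TDF-DP: no standard deviation, expected difference, cut-off or subset size. The only power statement touching adherence is the one carried over from the primary outcome (12 clinics, at least 100 participants each, 65% against 65 + 16 = 81%, ICC 0.05, power above 80%). Design effect = 1 + (100 − 1) × 0.05 = 5.95; effective n per arm = 6 × 100 / 5.95 = 100.8; two-sided power at 0.05 = 72.9%. The stated figure is therefore not reproduced at that ICC; it is reached at ICC 0.04 (80.4%). That is a separate matter. What counts here is that it assumes at least 100 measured participants per clinic, which does not describe a retrospectively chosen subset.

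**2. Information kept after a binary split.** Assume the log level is normal and the groups differ by a small shift. With a share p on one side of the cut and z the matching normal quantile, the efficiency of the binary analysis relative to the continuous one is φ(z)² / [p(1 − p)].

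| Split | Calculation | Kept | Lost | Required n multiplied by |
|---|---|---|---|---|
| 50/50 | 0.3989² / 0.25 | 0.637 | 36% | 1.57 |
| 65/35 | 0.3704² / 0.2275 | 0.603 | 40% | 1.66 |
| 80/20 | 0.2800² / 0.16 | 0.490 | 51% | 2.04 |
| 90/10 | 0.1755² / 0.09 | 0.342 | 66% | 2.92 |

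In power terms, a continuous analysis with 80% power falls to Φ[(1.960 + 0.842) × √0.637 − 1.960] = 61% at a median cut, and to 59% and 50% at 65/35 and 80/20. The splits are illustrative, since the article gives none.

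**3. Selection on viral load.** Take the planning values of 65% and 81% suppressed. Assume, for illustration only, that 85% of suppressed and 40% of unsuppressed participants are adherent by drug level, in both arms.

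- Everyone measured: control 0.65 × 0.85 + 0.35 × 0.40 = 0.6925; intervention 0.81 × 0.85 + 0.19 × 0.40 = 0.7645; risk ratio 1.10.
- Equal numbers of suppressed and unsuppressed, drawn from both arms together: suppressed participants are sampled at (0.35 + 0.19) / (0.65 + 0.81) = 0.370 times the rate of the others. The proportions become 0.583 and 0.675; risk ratio 1.16.
- Equal numbers drawn within each arm: (0.85 + 0.40) / 2 = 0.625 in both arms; risk ratio 1.00.

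The same data can thus show an inflated effect or none, depending on the sampling scheme. Weighting each sampled participant by the inverse of the sampling probability restores 0.6925 and 0.7645. Leaving the level continuous does not remove the distortion. A comparison of levels between the two viral load groups does not need these weights, if sampling depends only on viral load status.

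**The case against.** The strongest reply is that the article is a condensed document and defers detail to an SAP that is not shown. An assay cut-off is the kind of detail that belongs there, so its absence is no fault. The exploratory list speaks of alternate thresholds, which implies that a base threshold is intended; with one, adherence is binary and the log-binomial GEE can be fitted. The plan also allows methods to be revised after distributions are reviewed. All of this stands. A reader might infer that TDF-DP cannot be analysed as the plan is written, and the documents do not support that.

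A reader might also infer that the cut-off will be chosen to suit the results. That is not supported either. The alternate thresholds are labelled exploratory, staff analysing data are blinded to arm (Randomization and blinding), and preliminary analyses may well mean formative-phase work. The phrase is ambiguous, which calls for clarification and no more.

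Finally, splitting at an interpretable threshold costs efficiency but is a legitimate choice, and the general sentences may have been written with the Wilson measure in mind. That is probably so. But what the article does fix, rather than defer, is the endpoint type and the model. An SAP that follows them must cut the level and compare arms; one that does neither departs from the published text.

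**Conclusion.** The point holds in a limited form. The sentences declaring endpoints binary and secondary endpoints analysed identically do not fit TDF-DP, on two counts: it is a concentration, and it is taken in a subset selected on viral load and described as a comparison by viral load status. Following those sentences would discard about 36% of the information at best. That figure rests on an assumed normal log level and a small shift, and values below the assay limit would weaken the normality assumption. It is a general result: the range of 36% to 66% in the table should not be read as this trial's loss, which the documents do not allow anyone to compute. The risk ratios of 1.16 and 1.00 against a true 1.10 likewise rest on assumed adherence proportions and show only that the sampling matters. The point is a worthwhile improvement to a secondary measure.

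**What to change.** - In Statistical analysis, exempt TDF-DP from the two general sentences.
- State the contrast. If it is by viral load status, as Effectiveness outcomes words it, say so, and note that this does not by itself estimate the strategy's effect on adherence, which the Wilson measure would then carry. If it is by arm, use inverse sampling-probability weights and record the sampling fractions.
- Make log TDF-DP the main form: geometric mean ratio with 95% CI, clustered by site, with a stated rule for values below the assay limit. Keep an adherent/non-adherent summary as supportive.
- In the exploratory list, say that alternate adherence thresholds are fixed from formative-phase or external data before any post-intervention adherence or TDF result is viewed.
- Align Populations for analyses and the adherence power paragraph by limiting them to the Wilson measure, or by describing the TDF subset separately.

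The cost is wording and one extra model, with no new samples or participants. The downside is an effect measure less familiar to readers than a risk ratio.
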